### Study Layout

After recruitment, at month 0 (before exposure) and month 5 (after exposure), the participants will undergo a four-phased procedure:

Preparation: the trials will be explained to the participants and consent will be retrieved; any questions will be properly addressed;Familiarization: a test procedure will be performed where participants walk freely over the platform, without recording baropodometric gait analysis (BGA), to achieve the greatest possible freedom of movement. Participants will be asked to always walk barefoot.Trials: three types of gait protocols are usually applied in this type of study (one-step, two-step and mid-gait protocol). The choice should be based on both the variable of interest and the site of the foot to be studied. According to some authors (25, 26), there are few differences between the mid-gait (the *standard* protocol) and the two-step protocol, with similar values provided by both. An important criterion is using the same protocol throughout all studies, including follow-up.In this study, we chose to use the mid-gait protocol (Figure 1), particularly because the two-step termination protocol method is usually more appropriate for collecting joint kinematic data, which is out of the scope of this study, and also because the two-step initiation and termination protocols might delay acquiring the usual walking velocity during the trial (25, 26). In this sense, subjects will walk, at a self-selected pace, along an 8.0 m walkway. An initial position will be pre-established, to allow the right foot to hit the pedography platform at the middle of the walkway, with the fourth step, also avoiding gait alterations. After striking the platform, subjects will continue walking for 4.0 m until de end of the walkway.Additionally, participants will perform three valid trials per foot, as it has been previously found to be sufficient to ensure adequate reliability of force and pressure data (27–29) and will perform at least three steps before and after the pedography platform, as stated by Cousins et al. (27), that gait protocols should ideally involve a minimum preamble of at least three steps for a representative gait pattern to be obtained.It should be noted that a valid trial of a foot scan is defined as the participant hitting with the whole foot over the platform, without gait pattern alterations. A trial will be excluded, and should therefore be repeated, if a participant: (i) targets the borders of the platform with any part of the foot; (ii) alters gait to ensure full contact of the foot; and (iii) pauses on the mat.Self-Assessment of Foot Health: at the end of the BGA, participants will be asked to answer a self-assessment instrument about their current foot health, including skin, nail and presence of pain and will participate in a focus group together with another 5–10 participants from the study to discuss the influence of foot health in quality of life.

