**Kinetic variables**	Initial peak vGRF	vGRF consists of the ground reaction force during walking, this is, the force exerted by the ground on the body (the sum of all forces that exist between a body and the supporting surface). Abnormal peaks or loading values can lead to overuse injuries. vGRF can be measured in different gait phases, like initial, breaking or propulsive stances. It's measured in Newtons (N).
	Breaking vGRF	
	Propulsive vGRF	
	Peak plantar pressure	Foot plantar pressure is described as the distribution of forces exerted in the field between the sole of the foot and the ground. It's measured in kilopascal (kPa).
	COP displacement (medio-lateral)	In biomechanics, COP is the specific point where the vGRF vector is applied. Its displacement consists of an oscillation, which might be identified in different axis of the body in relation to the ground.
	COP displacement (anterior-posterior)	

*ROM, range of motion; vGRF, vertical Ground Reaction Force; COP, center of pressure*.

This outcome includes foot posture and foot function assessments, which are relevant biomechanical measures, that can be extracted from the plantar pressure scans acquired previously.

Foot posture can be characterized using the modified arch index (MAI), which is calculated by the division of the foot length, minus the toes, in three equal portions, and also the division of pressure in the middle third by that of all three regions.

Foot function is characterized by the center of pressure excursion index (CPEI), which is a measure of foot function throughout the gait cycle, being defined as the distance between an imaginary line drawn from the first and last points of each foot's center of pressure (COP) trajectory and the COP as the distal third tertile of the foot. This value is usually normalized by foot width and multiplied by 100, to obtain a percentage excursion of the COP.

Following previous similar studies (7), CPEI and MAI's distribution are divided into quintiles. For the first, feet in the top and bottom quintile will be considered as having a supinated and pronated foot function, respectively, and for MAI, the top and bottom 20% will be considered *pes planus* and *pes cavus*, respectively.

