### Statistical Analysis

The primary outcomes and the Foot Self-Care Knowledge (secondary outcome) will be analyzed using SPSS Statistics v25, namely with descriptive statistics (average; standard deviation; medians) with an *a priori* significance value of *p* < 0.05.

After verifying the type of distribution of the sample, using the Kolmogorov-Smirnov (KS) with Liliefors correction (suitable for samples with more than 30 subjects) (30), either the independent samples *t*-test (normal distribution) or the Mann-Whitney (test non-normal distribution) will be used to compare changes in outcomes before and after the exposure.

To relate variables of interest, namely podiatric profile variables and specific foot-health parameters, a Multiple Linear Regression will be computed and multivariate analysis of variance with repeated measures to detect significant interactions between variables.

To control confounding effects, we'll perform a stratification of variables, and evaluate the exposure-outcome association, also using Mantel-Haenszel (M-H) estimator for an adjusted result. Additionally, the Analysis of Covariance (ANCOVA) will be computed to assess the effect of certain factors on the outcome variables.

The secondary outcome, related to the students' perceptions, will be analyzed using ATLAS.ti v7 software, based on the content analysis as defined by Bardin (31). The different phases of analysis are: (i) pre-analysis; (ii) exploration of the material; and (iii) treatment of results, inference and interpretation. The categorical organization of the content will be performed *a posteriori*, through the following codification steps: (i) cutting—choice of units; (ii) enumeration—choice of counting rules; and (iii) classification and aggregation of chosen categories and units.

Potential missing data will be handled using marginal mean imputation, this is, computing the mean of the missing value, *X*, using the non-missing values and use it to impute missing values of *X*.

Regarding loss to follow-up, all data belonging to participants that choose to opt-out or are lost during the study, will be erased from storage, as explained in the informed consent document.

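### Feet are measured and classified, but the regression, Mantel-Haenszel and ANCOVA analyses make no provision for two feet per student; if feet are the rows, their standard errors are too small

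*Protocol article*

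**What the plan says.** All references are to the protocol article.

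- **Study Layout.** "participants will perform three valid trials per foot", which implies both feet. The same section fixes the starting position "to allow the right foot to hit the pedography platform at the middle of the walkway" and describes no equivalent for the left foot.
- **Exposures, Outcomes and Confounders.** CPEI is built from "the first and last points of each foot's center of pressure (COP) trajectory". The distribution is cut into quintiles, and "feet in the top and bottom quintile will be considered as having a supinated and pronated foot function, respectively". The same sentence labels the top and bottom 20% of MAI as planus and cavus. The S-FHAI is completed by the participant.
- **Participants and Recruitment Process.** The sample size counts students: 169 needed, 194 to be recruited.
- **Statistical Analysis.** To relate podiatric variables to foot-health parameters, "a Multiple Linear Regression will be computed", together with "multivariate analysis of variance with repeated measures to detect significant interactions between variables". Confounding is handled by stratification, "also using Mantel-Haenszel (M-H) estimator for an adjusted result", and by ANCOVA. The rule for change over the clinical training period reads, in part: "either the independent samples *t*-test (normal distribution) or the Mann-Whitney (test non-normal distribution) will be used to compare changes in outcomes before and after the".

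The article does not say whether the row of analysis is the student or the foot, or how two feet of one student are combined.

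**The concern.** Ranking feet into quintiles presupposes a data set with one row per foot. Multiple linear regression, ANCOVA and the Mantel-Haenszel estimator treat rows as independent. The two feet of one student are not independent: they share body weight, gait, ward and shifts, and the student's single set of questionnaire answers. A foot-level data set therefore enters each student twice.

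The link between podiatric profile and signs and symptoms is a stated aim of the study. If that link, and its adjustment for ward or activity, is tested on feet as independent units, confidence intervals are too narrow and associations are declared too often.

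**Working it through.** **The plan's own figure.** A single proportion of 50%, 95% confidence, 5% margin and a population of 300, with finite-population correction:

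- n0 = 1.96² × 0.25 / 0.05² = 384.15
- n = 384.15 / (1 + 383.15/300) = 168.7, rounded up to 169
- 169 × 1.15 = 194.35, so 194

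Both stated figures reproduce. They count students, so this point does not change them. Two feet from 169 students give 338 feet.

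**Inputs.** The 0.05 level is the article's; two-sided testing is assumed because sidedness is not stated. Every correlation below is an assumption, since the article gives none.

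**(a) Student-level covariate (such as ward type or a questionnaire score), feet as rows.** With between-foot correlation ρ, the design effect is 1 + ρ. Naive/true SE = 1/√(1 + ρ). Actual alpha = 2 × [1 − Φ(1.96 × naive/true SE)]. Effective feet = 338/(1 + ρ).

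| ρ | Design effect | Naive/true SE | Actual alpha | Effective feet |
|---|---|---|---|---|
| 0.3 | 1.3 | 0.877 | 0.086 | 260 |
| 0.5 | 1.5 | 0.816 | 0.110 | 225 |
| 0.7 | 1.7 | 0.767 | 0.133 | 199 |
| 0.8 | 1.8 | 0.745 | 0.144 | 188 |

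**(b) Foot-level covariate, feet as rows.** The design effect for the slope is 1 + ICC_x × ICC_y.

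| ICC_x | ICC_y | Design effect | Naive/true SE | Actual alpha |
|---|---|---|---|---|
| 0.3 | 0.5 | 1.15 | 0.933 | 0.068 |
| 0.5 | 0.5 | 1.25 | 0.894 | 0.080 |
| 0.7 | 0.7 | 1.49 | 0.819 | 0.108 |

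**(c) The named independent-samples before/after test, feet as rows.** This test ignores both the pairing of feet within a student and the pairing of month 0 with month 5. Let r_time be the correlation of the same foot over time, r_feet that of the two feet at one visit, and r_cross that of opposite feet at different visits. The mean change over n students has true variance proportional to [(1 − r_time) + (r_feet − r_cross)]/n, and the naive variance is proportional to 2/(2n) = 1/n. Hence true/naive variance = (1 − r_time) + (r_feet − r_cross). The naive SE is too small only if r_feet > r_time + r_cross. The last column is a simulation (10,000 runs, 169 students) of a paired t-test on feet.

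| r_time, r_feet, r_cross | True/naive variance | Naive/true SE | Actual alpha, named test | Actual alpha, paired test on feet |
|---|---|---|---|---|
| 0.7, 0.6, 0.5 | 0.40 | 1.58 | 0.002 | 0.089 |
| 0.5, 0.7, 0.4 | 0.80 | 1.12 | 0.028 | 0.117 |
| 0.2, 0.8, 0.15 | 1.45 | 0.83 | 0.10 | 0.143 |

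So the named test can err in either direction. Repairing only the time pairing leaves the between-foot problem, which then always acts towards too many rejections in these settings.

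**The case against.** The strongest reply is that foot-level analysis is inferred. The Statistical Analysis section names no row unit and does not mention the quintile labels. The t-test and linear regression need a continuous outcome, so the labels could not be their dependent variable. The sample size and the S-FHAI are per student, which fits a student-level analysis. Averaging the feet, or using one, would remove the problem without contradicting the text, and such detail is often left to an analysis plan that is not shown here.

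Much of this stands, and it makes the point conditional. It does not remove it: the article defines the podiatric measures and classes per foot, commits to methods that assume independent rows, and states neither an average nor a single foot.

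Four stronger readings are tempting, and the article does not support them:

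- *Every named method assumes independence.* The repeated-measures MANOVA does not. It is named only for interactions, has no foot factor, and does not repair the other analyses.
- *All standard errors are too small, including those for the primary change outcome.* Under the named before/after test, strong correlation over time makes the standard error too large.
- *The error rate is 11% to 14% in general.* That range belongs to a student-level covariate with an assumed correlation of 0.5 to 0.8.
- *Both feet are certainly scanned.* The call for trials on each foot implies it, but the right-foot set-up sits uneasily with it.

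**Conclusion.** The point holds in conditional form. If feet are the rows, as the quintile classification implies, the regression, Mantel-Haenszel and ANCOVA analyses understate their standard errors. For a student-level covariate and an assumed between-foot correlation of 0.3 to 0.8, naive/true SE is about 0.88 to 0.75 and actual alpha about 0.09 to 0.14. For a foot-level covariate (assumed ICC_x 0.3 to 0.7, ICC_y 0.5 to 0.7), actual alpha is about 0.07 to 0.11. No direction can be claimed for the independent-samples before/after comparison. If the analysis uses one value per student, the between-foot problem disappears, but the article does not say so. Separately, the right-foot set-up and the call for trials on each foot need to be reconciled.

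**What to change.** 1. Reconcile the right-foot set-up with the trials on each foot, and state which feet are scanned.
2. State the unit of analysis, and average the three valid trials per foot before any modelling.
3. If both feet are kept, analyse podiatric outcomes with a mixed model, GEE or cluster-robust standard errors by student, with foot and visit within student. Use this for the change from month 0 to month 5 and for the association and confounder analyses.
4. Otherwise, analyse one pre-named foot or the mean of both feet per student, with paired methods for change.

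The cost is analysis wording and no new data. Compared with treating feet as independent, confidence intervals for a student-level covariate widen by a factor of √1.3 = 1.14 to √1.8 = 1.34 over the assumed range. For a foot-level covariate the widening is √1.15 = 1.07 to √1.49 = 1.22.

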
**Figure 1 F1:**
[figure not shown]
Midgait method. Participants start 4.0 m from the platform (P) [Adapted from Wearing et al. (25)].

### Instruments

To record the desired data, the Emed^®^ platform from *novel.de* will be used. It consists of a pedography platform to measure pressure distribution under the foot, containing calibrated capacitive sensors, with the potential to accurately measure foot pressure in static and dynamic positions.

The main variables measured (throughout time) are: maximum pressures, pressure/time, force exerted, contact area and COP line.

According to the provider, the sensor platform has an area (mm) of 475 × 320 with a total of 6,080 sensors, with a resolution (sensor/cm^2^) of 4. The recording frequency is set at 50 Hz, with a pressure range (kPa) of 10–1.270. The pressure threshold is 10 kPa and the maximum total force is 193,000 N.

### Statistical Analysis

The primary outcomes and the Foot Self-Care Knowledge (secondary outcome) will be analyzed using SPSS Statistics v25, namely with descriptive statistics (average; standard deviation; medians) with an *a priori* significance value of *p* < 0.05.

After verifying the type of distribution of the sample, using the Kolmogorov-Smirnov (KS) with Liliefors correction (suitable for samples with more than 30 subjects) (30), either the independent samples *t*-test (normal distribution) or the Mann-Whitney (test non-normal distribution) will be used to compare changes in outcomes before and after the exposure.

To relate variables of interest, namely podiatric profile variables and specific foot-health parameters, a Multiple Linear Regression will be computed and multivariate analysis of variance with repeated measures to detect significant interactions between variables.

To control confounding effects, we'll perform a stratification of variables, and evaluate the exposure-outcome association, also using Mantel-Haenszel (M-H) estimator for an adjusted result. Additionally, the Analysis of Covariance (ANCOVA) will be computed to assess the effect of certain factors on the outcome variables.

The secondary outcome, related to the students' perceptions, will be analyzed using ATLAS.ti v7 software, based on the content analysis as defined by Bardin (31). The different phases of analysis are: (i) pre-analysis; (ii) exploration of the material; and (iii) treatment of results, inference and interpretation. The categorical organization of the content will be performed *a posteriori*, through the following codification steps: (i) cutting—choice of units; (ii) enumeration—choice of counting rules; and (iii) classification and aggregation of chosen categories and units.

Potential missing data will be handled using marginal mean imputation, this is, computing the mean of the missing value, *X*, using the non-missing values and use it to impute missing values of *X*.

Regarding loss to follow-up, all data belonging to participants that choose to opt-out or are lost during the study, will be erased from storage, as explained in the informed consent document.

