### Exposures, Outcomes and Confounders

The exposure under study consists of a particular environment that poses particular biomechanical risks to the foot/ankle region. According to Bernardes et al. (15), standing environments include those of prolonged standing and prolonged walking, which can be defined as spending at least 5% of occupational time standing or walking (21).

The first primary outcome of interest is related to the change in podiatric profile at 5 months and will be evaluated at month 0 and month 5, being an objective and quantitative outcome. In this case, specific foot-related variables while walking will be recorded, illustrating the actual behavior of the foot during activity. The assessment of the podiatric profile follows the important premise that the medial longitudinal arch is one of the most important and highly variable structural characteristic of the human foot (22).

The relevant variables that describe this outcome are summarized in Table 1.

**Table 1 T1:** Specific podiatric profile variables.

**Category**	**Variables**	**Definition**
**Kinematic variables**	Forefoot width/spreading	Distance, in millimeters, between two straight lines perpendicular to the Chopart joint and tangential to most medial and most lateral points of the heads of first and fifth metatarsals, respectively.
	Foot angle at contact (sagittal plane)	Dorsiflexion angle at contact, in relation to the sagittal plane.
	Foot eversion	Or pronation, is an angular movement where the foot moves away from the medial plane.
	Foot adduction	Is the angular movement were the foot moves toward the medial plane.
	Foot external rotation	Rotation of the joint away from the midline, measured as an angle.
	Ankle inversion	Angular movement toward the medial plane.
	Medial longitudinal arch (MLA)	Located between the heel proximately and the medial three metatarsophalangeal joints anteriorly. Runs through metatarsals 1-3, sesamoid bones, cuneiform bones, navicular, talus, and calcaneus bones; the plantar aponeurosis, spring ligament, talocalcaneal ligament, and deltoid ligament; the flexor *hallucis longus*, flexor *digitorum longus, abductor hallucis*, flexor *digitorum brevis*, tibialis posterior.
	Ankle plantarflexion ROM in late stance	Refers to the angular distance of the movement around the ankle joint during the late stance of gait, characterized by a single limb support, and occurring before the swing period.

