Another variable of interest to characterize the podiatric profile is plantar loading characteristics. As there is no current consensus in the literature for the definition of adequate foot segments, this study will consider the templates of similar studies, which showed good reliability for plantar forces and pressures during barefoot walking in healthy adults (23). Namely, the regions to assess and compare are: lateral heel, medial heel, midfoot, 1st metatarsophalangeal joint (1MPJ), 2nd−5th metatarsophalangeal joint (2–5MPJ), hallux and the lesser toes.

The second primary outcome concerns the change in foot health at 5 months, a subjective evaluation by the participant, and is related to observed clinical parameters, signs and symptoms, namely skin, nails, foot structure, as well as presence and location of the pain. The Portuguese adaptation of the Self-Administered Foot Health Assessment Instrument (S-FHAI), a Likert-type instrument with four dimensions, will be used. It will be applied at month 0 and month 5. The majority of observed foot disorders will be recorded as either present or absent.

The study also includes the following secondary outcomes: (i) Foot Self-Care Knowledge, which is assessed between month 0 and month 5, through a four-dimensional questionnaire, where specific interventions for the promotion and prevention of foot and ankle disorders are evaluated; and (ii) Students' perceptions about the influence of foot health in their quality of life. It is evaluated through focus groups after exposure time (month 5).

Regarding potential effect modifiers and confounders, we expect that different nursing activities and ward typology (e.g., surgical units, intensive care) might produce diverse baropodometric patterns.

The primary and secondary outcomes, respective instruments for evaluation and timeframes for assessment are summarized in Table 2.

**Table 2 T2:** Primary and secondary outcomes assessment.

			**Assessment**	**Timeframe**		
				**Month 0**	**Month 3**	**Month 5**
**Primary Outcomes**	Change in Podiatric Profile at 5 months^*^	Kinematic variables	EMED® software	x		x
		Kenetic variables		x		x
		Foot posture	MAI analysis	x		x
		Foot function	CPEI analysis	x		x
	Change in Foot Health at 5 months	Skin health	Portuguese adaptation of the self-administered foot health assessment instrument [S-FHAI; (24)].	x		x
		Nail health		x		x
		Foot structure		x		x
		Foot pain		x		x

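### A normality pre-test decides whether the before/after comparison uses means or ranks, without naming the within-student change, and both branches ignore pairing

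*Protocol article*

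**What the plan says.** In the Protocol article, Statistical Analysis, the scope is set first: "The primary outcomes and the Foot Self-Care Knowledge (secondary outcome) will be analyzed using SPSS Statistics v25", "with an *a priori* significance value of *p* < 0.05". The gate follows: "After verifying the type of distribution of the sample, using the Kolmogorov-Smirnov (KS) with Liliefors correction". Its outcome selects the test, which is an independent-samples t-test where the data pass as normal, "or the Mann-Whitney (test non-normal distribution) will be used to compare changes in outcomes before and after the exposure".

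The design is one cohort measured twice. Under Study Layout, "at month 0 (before exposure) and month 5 (after exposure), the participants will undergo a four-phased procedure". Under Exposures, Outcomes and Confounders, the first primary outcome is the "change in podiatric profile at 5 months and will be evaluated at month 0 and month 5, being an objective and quantitative outcome". The second is a Likert-type self-report of foot health, of which the same section says "The majority of observed foot disorders will be recorded as either present or absent".

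The text does not say which values enter the normality test (month 0, month 5, pooled or change). It gives no separate level for that test and fixes no test in advance for any primary variable.

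**The concern.** A t-test concerns a difference in means; a rank test does not. When a pre-test on the same data picks between them, the hypothesis is settled only after the data are seen. The primary outcomes contain many variables: the kinematic and kinetic lists of Table 1, the arch index, the centre-of-pressure index, seven plantar regions and the foot-health dimensions. Some primary results could be statements about mean change and others about ranks, with no scientific reason for the split.

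Three things are at stake:
- whether the gate protects anything at this sample size;
- whether it looks at the quantity that matters for a before/after question, which is each student's change;
- whether either of the two tests suits two measurements on the same student.

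**Working it through.** **Inputs.** From the article: 300 students per year, 95% confidence, 5% margin, 50% proportion, n = 169, 15% added to reach 194, significance level 0.05. Assumed, because the article gives none: two-sided tests, 0.05 as the level of the pre-test, the shapes of the distributions, the month 0 to month 5 correlation (0.5 to 0.9) and a shift of 0.2 SD.

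**1. The plan's own figure.** n0 = 1.96² × 0.5 × 0.5 / 0.05² = 384.2. With the finite population correction, n = 384.2 / (1 + 383.2/300) = 168.7, so 169. Then 169 × 1.15 = 194.35, so 194. Both reproduce. They rest on the precision of one proportion, so no change of test alters them.

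**2. Does the gate protect anything?** Changes with true mean 0 were drawn from centred gamma distributions (skewness = 2/√shape; shapes 16, 8, 4), n = 169. Ranges are over three separate simulations.

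| Skewness of change | Lilliefors rejects | t-test on the change rejects |
|---|---|---|
| 0.5 | 29–36% | 4.4–5.8% over all |
| 0.7 | 55–63% | three settings |
| 1.0 | 87–92% | and simulations |

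Other shapes give the same picture. Heavy tails (t with 5 df): the gate fires in 49%, t-test error 4.9%. A rounded 0–10 score (an assumed scale): 100% and 4.9%. Skewness about 2.2: 100% and 5.7%. A truly normal variable still goes to ranks about 5% of the time.

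**3. Does it matter which values are checked?** With skewed student levels (assumed lognormal) but normal changes, and within-student correlation 0.5 / 0.7 / 0.9, the gate rejects the month 0 values in 35% / 73% / 97% of samples and the changes in about 5%. The reverse case, skewed changes on a normal baseline, gives rejection of raw month 5 values in about 4–12% / 4–19% / 5–36% at skewness 0.5 / 0.7 / 1.0, well below the rates in step 2. These are alternative readings of the same sentence and cannot both apply, so the branch taken depends on something the text leaves open.

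**4. What does ignoring pairing cost?** With correlation ρ, the mean difference has variance 2σ²(1−ρ)/n, but the independent t-test divides by √(2σ²/n).
- Type I error ≈ 2·P(Z > 1.96/√(1−ρ)).
- Power of the independent t-test for 0.2 SD ≈ P(Z > (1.96 − 0.2√(169/2))/√(1−ρ)), with 0.2√84.5 = 1.838.
- Power of the paired t-test ≈ P(Z > 1.96 − 0.2√169/√(2(1−ρ))), with 0.2 × 13 = 2.6.

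| ρ | Type I, independent t | Power, independent t | Power, paired t |
|---|---|---|---|
| 0.5 | 0.006 (simulated 0.007) | 0.43 (0.42) | 0.74 (0.72) |
| 0.7 | 0.0003 (0.0003) | 0.41 (0.40) | 0.92 (0.91) |
| 0.9 | below 0.0001 (0.000) | 0.35 (0.38) | 1.00 (1.00) |

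Simulated type I error of Mann-Whitney in the same settings is 0.013, 0.004 and 0.000. Other simulations put the unpaired power at about 0.36–0.48 against 0.75–1.00 for the paired t-test, which is the same conclusion.

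**5. Do ranks produce false positives?** On changes with mean 0 and skewness 0.5 / 0.7 / 1.0, a signed-rank test rejects in about 7–10% / 11–12% / 18–20%; at skewness about 2.2 it rejects in 52%, against 6% for the t-test. The plan does not name that test. Mann-Whitney, the test it does name, rejects in 0–1.7% / 0–2.4% / 0–4.9% when the same changes are added to a normal baseline with SD 0.7 to 2 times that of the change.

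**The case against.** Normality pre-testing is common practice, and a journal article may leave the values checked and the level of the pre-test to a fuller document. That is fair for those details. It does not cover the rule itself, which the article states: the result of the pre-test selects the type of test.

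A reader might infer more than the text supports:
- **That the wrong distribution is checked.** The wording is ambiguous, and the same sentence speaks of changes in outcomes. If changes are what is tested for normality, this criticism falls away. What can be shown is only that the within-student change is not named.
- **That the plan as written inflates false positives.** The excess rejections in step 5 belong to the signed-rank test. The named Mann-Whitney test is conservative here because it ignores pairing. The excess would arise only if the tests were made paired and the gate were kept.
- **That the gate is explicitly applied to each variable.** This is not written. It is the natural reading, because the test is univariate and the variables are many.

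The section also lists a repeated-measures multivariate analysis, which does respect pairing. Its stated purpose is to detect interactions between variables; the before/after comparison is assigned to the two independent-group tests.

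Finally, pairing is the larger error in the sentence. That stands, and for that reason the two are treated together: correcting the pairing alone would leave the gate in place, and dropping the gate alone would leave an unpaired test.

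**Conclusion.** The point holds in this form. The stated rule lets the data choose between a mean-based and a rank-based comparison, does not name the within-student change as the distribution checked, and offers only tests for independent groups in a design that measures the same students twice.

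The gate is unnecessary at n about 169. It fires in roughly 30 to 90% of samples at skewness 0.5 to 1.0, where a t-test on the change is already accurate. The main loss under the plan as written is power: for a 0.2 SD shift, about 0.4 for the independent t-test against about 0.7 to 1.0 paired. These sizes rest on the assumed distributions, correlations and shift, none of which the article gives. The direction of the pairing result needs only a positive correlation between a student's two measurements. The point is worth correcting before analysis, and it does not touch the recruitment target.

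**What to change.** Delete the normality gate and both independent-group tests from the before/after comparison. In their place:
- For every continuous primary variable, prespecify the mean within-student change (month 5 minus month 0) with its 95% CI and a paired t-test, the same for all variables.
- Report a bootstrap CI and a signed-rank test as sensitivity checks only; neither replaces the primary result.
- Analyse present/absent foot-health items with a paired binary method such as McNemar's test.
- Analyse Likert-type foot-health items with one paired method named in advance.

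The cost is a few sentences of analysis wording, with no new data and no change to 169 or 194. Fixing the mean change is a choice of what to estimate, so the investigators should confirm that it is the quantity they want. The statistical downside is a small loss of power for very heavy-tailed variables.
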